**2.5.3 Participants**

Participants recruited in Phase 1 will be eligible for Phase 3. Inclusion and exclusion criteria will be reconfirmed at the time of enrolment into Phase 3. Participants who have developed new contraindications to yoga or MRI during the Phase 1 to Phase 3 interval will be excluded.

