**2.3.3 Inclusion criteria**
•Age 60–80 years, both sexes.•Clinical diagnosis of type 2 diabetes mellitus for the obese-diabetic group.•Body mass index (BMI) ≥ 25 kg/m
^2^ as per Asia-Pacific guidelines for obesity classification.
^
25
^
•Able to provide written informed consent independently or through a legally authorized representative.

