**2.3.5 Sample size**

Sample size was estimated using G*Power 3.1 software. A multivariate analysis of variance (MANOVA) power analysis was performed with an assumed medium effect size (f
^2^ = 0.25), a significance level of α = 0.05, and a desired statistical power of 0.80. This yielded a minimum total sample of 80 participants. Accounting for anticipated attrition and protocol deviations, 40 participants will be recruited to each group (obese-diabetic and obese-non-diabetic), yielding a total of 80 participants for Phase 1.

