**2.4.1 Objective**

The objective of Phase 2 is to develop and content-validate a structured yoga module tailored to the physiological capabilities, safety requirements, and therapeutic needs of elderly adults with comorbid obesity and T2DM.

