**2.5.1 Objective**

Phase 3 aims to investigate the effects of the validated structured yoga module on vascular health, structural and functional brain networks, and cognitive function in elderly adults with comorbid obesity and T2DM, using multimodal MR neuroimaging before and after a 6-month intervention period.

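### The Phase 3 eligibility rule does not exclude the non-diabetic half of Phase 1, although the Phase 3 objective and the yoga module concern adults with both obesity and T2DM

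*Protocol article*

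**What the plan says.** All references are to the protocol article.

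- **Who may enter Phase 3 (2.5.3 Participants).** "Participants recruited in Phase 1 will be eligible for Phase 3". The further filters are that "Inclusion and exclusion criteria will be reconfirmed at the time of enrolment into Phase 3" and that people with new contraindications to yoga or MRI are left out. No T2DM requirement specific to Phase 3 is added.
- **Who is in Phase 1 (2.3.5 Sample size).** "40 participants will be recruited to each group (obese-diabetic and obese-non-diabetic), yielding a total of 80 participants for Phase 1".
- **The T2DM criterion (2.3.3 Inclusion criteria).** "Clinical diagnosis of type 2 diabetes mellitus for the obese-diabetic group".
- **What Phase 3 is for (2.5.1 Objective).** The effects of the module on vascular health, brain networks and "cognitive function in elderly adults with comorbid obesity and T2DM, using multimodal MR neuroimaging before and after a 6-month intervention period".
- **Whom the module is built for (2.4.1 Objective).** It is tailored to the capabilities, safety requirements and "therapeutic needs of elderly adults with comorbid obesity and T2DM". The Discussion (section 5) likewise describes the yoga intervention as taking place in elderly obese-diabetic people.
- **How Phase 3 is analysed (2.5.8 and 2.5.10).** Every participant is reassessed after 6 months. Pre and post values are compared with paired tests. Mixed models adjust for age, sex, baseline physical activity, HbA1c and medication use.

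**The concern.** The eligibility section and the objective describe different populations. Staff enrol from the eligibility section, and its plain wording lets in every Phase 1 participant, including people without T2DM. The analysis section does not separate the two groups again.

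At stake is what the Phase 3 result describes. The article proposes that the findings feed into AYUSH guidance and community NCD programmes on the strength of benefit in obese-diabetic elders. A pre-post change averaged over people with and without T2DM supports that only if the two groups respond alike, and no planned analysis checks this. Adjusting for HbA1c does not settle it. That adjusts for a level; it neither restricts the sample nor lets the change over time differ by diabetes status. A T2DM-only set chosen after Phase 3 data are in would be a post hoc choice.

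**Working it through.** **Step 1. Does the rule as written let non-diabetic participants through?**

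| Filter | Source | Removes a non-diabetic Phase 1 participant? |
|---|---|---|
| Recruited in Phase 1 | 2.5.3 | No |
| Age, BMI and consent criteria | 2.3.3 | No, common to both groups |
| T2DM diagnosis | 2.3.3 | No, binds the obese-diabetic group only |
| Exclusion criteria | 2.3.4 | No, absence of T2DM is not listed |
| New contraindication to yoga or MRI | 2.5.3 | No, unrelated to diabetes status |

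The plan's own figures give the share of the eligible pool: 40 + 40 = 80, and 40/80 = 50% non-diabetic. This point does not depend on how the 80 was derived.

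**Step 2. What would a combined estimate be?**

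Let δ be the mean change in the T2DM group and rδ the mean change in the non-diabetic group. With equal numbers:

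combined change = 0.5δ + 0.5rδ = 0.5(1 + r)δ

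The documents give no value for r, so a range is shown:

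| r (assumed) | Combined change |
|---|---|
| 0 | 0.5δ |
| 0.5 | 0.75δ |
| 1 | δ |

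If r exceeded 1, the combined change would exceed δ. The direction is therefore open as well as the size.

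**Step 3. What would that do to power?**

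The article gives no Phase 3 effect size, so δ is an assumption. Take a change SD of 1 in each group. The SD of the mixture is then √(1 + 0.25(δ − rδ)²). Power of a two-sided paired t-test at 0.05 comes from the noncentral t distribution with n − 1 degrees of freedom and noncentrality d√n, where d is mean change divided by SD of change. For δ = 0.5 and r = 0: mean 0.25, SD √(1 + 0.25 × 0.25) = 1.031, d = 0.243.

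| δ | r | Combined mean change | Power, both groups, n = 80 | Power, T2DM only, n = 40 |
|---|---|---|---|---|
| 0.5 | 0 | 0.25 | 0.57 | 0.87 |
| 0.5 | 0.5 | 0.375 | 0.91 | 0.87 |
| 0.5 | 1 | 0.50 | 0.99 | 0.87 |
| 0.3 | 0 | 0.15 | 0.26 | 0.46 |
| 0.3 | 0.5 | 0.225 | 0.51 | 0.46 |
| 0.3 | 1 | 0.30 | 0.76 | 0.46 |

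Combining the groups can lower or raise power. What it changes in every case except r = 1 is the quantity being estimated.

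**Step 4. What does restricting to the T2DM group cost?**

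Solving the same power formula for d at 80% power:

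| n | Detectable change (SD of change) |
|---|---|
| 80 | 0.317 |
| 40 | 0.454 |
| 32 (40 less an assumed 20% loss: 40 × 0.8) | 0.511 |

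The 20% loss is an assumption; the article states no Phase 3 attrition rate.

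**The case against.** The best reply is that the intent is plain. The objective, the module, the Discussion and the repository title all point to obese-diabetic adults, and the eligibility sentence follows shortly after the objective. It may mean no more than that Phase 3 draws on Phase 1 participants who belong to the stated population. On that reading, the lack of a group term in 2.5.10 is natural. If both groups do enter, the group terms could be set in an analysis plan not shown here. This has force as to intent, and it means the analysis section cannot serve as independent proof of pooling. It does not remove the conflict: the sentence has no such limit, and the criteria it relies on do not supply one. An analysis plan could define a T2DM set, but could not make the eligibility rule agree with the objective.

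A reader might infer more than the documents support:

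- **That half of those practising yoga will be non-diabetic.** The text says eligible, not enrolled, and no passage states that non-diabetic participants will receive the module.
- **That the result will be pooled and will describe the wrong population.** Pooling is an inference from reassessing all participants and naming no group term. The article does not state it.
- **That the effect will be halved.** That is the r = 0 case only, and nothing in the documents supports that value over the others.
- **That the lack of a stated Phase 3 sample size is itself an error.** A condensed article may leave that to the full protocol.

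**Conclusion.** The contradiction holds with high confidence as a matter of text. Section 2.5.3 does not exclude the 40 non-diabetic participants out of 80, the re-check does not remove them, and the objective and module are for adults with obesity and T2DM.

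The consequence is conditional. If both groups enrol and are analysed together, the estimate is a mixture that matches the T2DM effect only if both groups respond alike. Its departure from that effect is unknown in size and direction; the range of 0.5δ to δ rests on equal numbers and an assumed relative response between 0 and 1. The point should be settled before Phase 3 enrolment because it determines who is studied in the intervention phase.

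**What to change.** Reconcile 2.5.3 with 2.5.1 before Phase 3 enrolment, by one of two routes.

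1. **Restrict.** State that only the Phase 1 obese-diabetic group is eligible for Phase 3, at most 40 people. This is one sentence and means fewer repeat scans. The price is sensitivity: the detectable paired change rises from about 0.32 SD at n = 80 to 0.45 SD at n = 40, or 0.51 SD if 20% are lost. It would help to state these figures alongside the rule.
2. **Keep both groups.** Widen the Phase 3 objective to say so, name the T2DM group as the primary analysis set for the objective as it now stands, and add group and group-by-time terms to the mixed model in 2.5.10. This costs an edit to the objective and one or two sentences of analysis. The primary T2DM estimate would still rest on at most 40 people, so the wider enrolment does not by itself buy back the sensitivity given up under route 1.

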**2.3.4 Exclusion criteria**
•Presence of neurological or psychiatric conditions known to affect brain morphology or cognitive function (e.g., Parkinson’s disease, major depressive disorder, schizophrenia, prior stroke or traumatic brain injury).•History of neurodegenerative disease (e.g., Alzheimer’s disease, vascular dementia).•Type 1 diabetes mellitus or secondary forms of diabetes.•Active malignancy or any systemic illness likely to confound neuroimaging or cognitive assessments.•Contraindications to MRI (metallic implants, claustrophobia, cardiac pacemakers).•Current or recent (within 6 months) regular yoga practice (≥ 2 sessions per week).•Severe hearing or visual impairment precluding cognitive testing.

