**Step 2: Integration and selection of practices**

Yoga practices identified as having therapeutic potential for vascular health, brain structural and functional improvement, and cognitive enhancement will be collated. These will be evaluated for their safety and practicability in the context of the target population’s physical limitations, comorbidities (osteoarthritis, reduced balance, cardiorespiratory deconditioning), and age-related contraindications to inversions, deep twists, and high-load postures. Selected practices will encompass asanas (physical postures), pranayama (breath regulation), and dharana/dhyana (mindfulness and concentration techniques).

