**Step 3: Adaptation and manual preparation**

Selected practices will be adapted to accommodate the functional capacity of elderly obese-diabetic individuals. Modifications will include the use of props (chairs, bolsters, straps), reduced range-of-motion variants, seated and supine alternatives to standing postures, and graded progressions. A structured yoga manual will be produced, containing illustrated instructions, duration and frequency specifications, contraindication notices, and safety guidelines. The manual will be bilingual (English and Kannada) to ensure accessibility in the local population.

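### The Phase 3 exclusion for yoga contraindications covers only new ones, although the Phase 1 criteria list none, so a long-standing contraindication passes both stated entry checks

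*Protocol article*

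**What the plan says.** Section 2.5.3 governs entry to Phase 3 in three sentences. The source population is the Phase 1 sample: "Participants recruited in Phase 1 will be eligible for Phase 3". The first check is a repeat of the eligibility criteria: "Inclusion and exclusion criteria will be reconfirmed at the time of enrolment into Phase 3". The second is an added exclusion: "Participants who have developed new contraindications to yoga or MRI during the Phase 1 to Phase 3 interval will be excluded".

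The only criteria that the article lists are those of Phase 1 (sections 2.3.3 and 2.3.4). Three of the exclusions bear on this point:

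- MRI safety: "Contraindications to MRI (metallic implants, claustrophobia, cardiac pacemakers".
- General illness: "Active malignancy or any systemic illness likely to confound neuroimaging or cognitive assessments".
- Yoga, as prior practice: "Current or recent (within 6 months) regular yoga practice (≥ 2 sessions per week".

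Section 2.4.2 places the safety work on the module in Phase 2. Step 2 evaluates practices against "comorbidities (osteoarthritis, reduced balance, cardiorespiratory deconditioning), and age-related contraindications to inversions, deep twists, and high-load postures". Step 3 adapts the chosen practices and produces a manual that contains "duration and frequency specifications, contraindication notices, and safety guidelines".

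**The concern.** An exclusion limited to what is new since an earlier time point works only if the older cases were removed at that time point. The rule treats yoga and MRI alike, but only MRI has such a starting screen. For yoga, the rule as written would exclude a participant whose contraindication appeared between the phases and admit one whose contraindication is older. The article gives no reason for treating the two differently.

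What is at stake is first the safety of obese adults aged 60 to 80 who are asked to do regular physical practice, mostly away from an instructor. A second consequence is statistical. People admitted despite being unable to perform the module would enter the single-group pre-post comparison of section 2.5.10 and could weaken the estimated change. If sites instead excluded them on judgement, those exclusions would depart from the written rule.

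**Working it through.** The check is mainly a reading of the criteria. It involves no sample size, power or alpha figure, and the plan has no figure of its own to reproduce.

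**Step 1. Four cases against the two Phase 3 checks.**

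| Contraindication | On the Phase 1 list (2.3.3, 2.3.4)? | New since Phase 1? | Outcome under 2.5.3 |
|---|---|---|---|
| MRI, predates Phase 1 | Yes | No | Excluded at Phase 1 and again on re-check |
| MRI, arises after Phase 1 | Yes | Yes | Excluded by both checks |
| Yoga, arises after Phase 1 | No | Yes | Excluded by the added rule |
| Yoga, predates Phase 1 | No | No | Passes both checks |

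Only the last row fails. For MRI, the word new adds nothing and removes nothing. For yoga, it decides the result.

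**Step 2. Could another Phase 1 criterion catch the last row?** The systemic-illness criterion is tied to confounding of imaging or cognition, not to fitness for exercise. The yoga criterion concerns recent regular practice. Prior stroke, Parkinson's disease and severe visual impairment may incidentally remove some people unfit for yoga, but they are set for imaging or cognitive reasons and do not amount to a screen.

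**Step 3. Could Phase 1 have screened against the module?** Not against its contraindication notices. The manual that carries them is a Phase 2 product (section 2.4.2, Step 3), and section 5 describes the three phases as sequential.

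**Step 4. Does anything after enrolment exclude?** Section 2.5.4 has a certified instructor demonstrate the practices and answer safety questions. Section 2.5.7 provides weekly messages. The manual carries notices. None of these is stated as a condition of entry.

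**Step 5. How much practice is outside the orientation?** Inputs: at least 5 days a week for 6 months (section 2.5.5), and an in-person orientation of about 60 minutes for the first 15 days (section 2.5.4). Six months is taken as 26 weeks.

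- Minimum sessions: 5 × 26 = 130.
- The orientation wording can mean one session or one a day for 15 days, so 1 to 15 in-person sessions.
- In-person share: 1/130 = 0.8% to 15/130 = 11.5%.
- Outside the orientation: at least 130 − 15 = 115 sessions, and 115/130 = 88%.

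That these sessions take place at home is an inference from delivery by manual and video with remote follow-up; the article does not name a place.

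**The case against.** The strongest reply is that the protocol answers long-standing limitations by adapting the practice, not by excluding the person. Section 2.4.2 provides props, smaller ranges of motion, seated and supine alternatives and graded progressions, and section 2.4.3 has the module validated by an expert panel. This stands, and it rules out one tempting inference. A reader might take the comorbidities in Step 2 to be contraindications to yoga that the Phase 3 rule lets through. The text does not say so: it uses those comorbidities to judge which practices are suitable, and the contraindications it names there are to types of posture. Adaptation still does not settle the point, because section 2.5.3 itself treats some contraindications to yoga as grounds for exclusion and then limits them to recent ones.

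A reader might also infer that the added rule is the only barrier before the intervention. It is not: the Phase 1 criteria are reconfirmed as well.

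A third reply is that a journal article condenses a fuller protocol, where a baseline yoga screen may be described. That is possible, and the article cannot show that no such screen exists. The point here is narrower. The article states an exclusion rule whose wording relies on an earlier screen, and its own criteria list does not contain one. That is a rule that misfires as written, not a detail left out.

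Finally, an investigator would probably not enrol someone with a known contraindication, whatever the sentence says. That lowers the likely harm but is a reason to correct the sentence, not to keep it.

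**Conclusion.** The point holds as a mismatch between sections 2.3.4 and 2.5.3. For MRI the two sections fit together. For yoga, a contraindication that predates Phase 1 passes both stated Phase 3 checks. Those admitted would do at least about 115 of a minimum of about 130 sessions outside the in-person orientation. That figure assumes a 26-week period, the minimum frequency, and the most generous reading of the orientation (15 in-person sessions). It describes how the module is delivered, not how often the gap would be met.

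Two stronger conclusions are not supported. The number of participants affected cannot be derived, because the article gives no prevalence of contraindications to yoga. The dilution of the pre-post change is plausible in direction, but nothing in the article allows its size to be calculated. The case for acting rests on participant safety and on how cheap the correction is, not on a demonstrated change in any estimate.

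**What to change.** Reconcile sections 2.3.4 and 2.5.3. In section 2.5.3, remove the restriction to new contraindications and to the interval between the phases, so that the Phase 3 check covers contraindications to MRI and to participation in the yoga module that are present at Phase 3 enrolment, whenever they arose.

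The rule should not automatically exclude anyone to whom some notice in the manual applies. Section 2.4.2 does not say whether the notices concern the whole module or single practices. If they concern single practices, such a rule could remove people whom the seated or modified variants are meant to accommodate. Which conditions count as a contraindication to taking part, and which are handled by an adapted variant, is for the investigators and the Phase 2 panel to decide and record before Phase 3 enrolment opens.

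The cost is one reworded sentence and an entry check at Phase 3. The Data Availability section states that no participant data had been collected at publication, so the change can be made in time. The downside is that some Phase 1 participants may not continue to Phase 3; the article does not allow that number to be estimated.

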**2.5.4 Intervention: delivery**

The structured yoga module validated in Phase 2 will be delivered to each participant as a printed bilingual manual accompanied by an illustrative video guide. An initial in-person orientation session (approximately 60 minutes for the first 15 days) will be conducted at CIMR, Manipal, during which a certified yoga instructor will demonstrate all practices, correct technique, and address safety questions.

**2.5.5 Intervention: frequency and duration**

Participants will be asked to practice yoga for at least 5 days per week for 6 months. Each session will be approximately 45–60 minutes in duration, incorporating a warm-up asana sequence (10 minutes), core therapeutic asanas (25–30 minutes), pranayama (10 minutes), and relaxation/dharana (5–10 minutes).

**2.5.6 Physical activity monitoring**

Objective physical activity will be continuously monitored throughout the 6-month intervention using an accelerometer worn on the dominant thigh during all yoga sessions and other physical activities. Participants will be instructed to wear the accelerometer throughout waking hours (except during bathing or water activities) and to activate a dedicated event marker button at the commencement and completion of each yoga session.

**2.5.7 Remote adherence monitoring**

To support adherence and participant retention, a dedicated remote monitoring protocol will be implemented. Research staff will contact participants weekly via their preferred messaging platform (WhatsApp or SMS) to enquire about yoga practice status, address queries, and provide motivational support. Participants will also be encouraged to use commercially available mobile fitness-tracking applications (e.g., Google Fit) or wearable fitness devices (e.g., smartwatches) to self-monitor daily physical activity. Participants will maintain session logs in a structured diary provided at enrolment.

**2.5.8 Post-Intervention assessment**

Following the 6-month intervention period, all participants will undergo a complete repeat of the neuroimaging protocol and cognitive assessments as described in Phase 1. Physical activity, anthropometric, and metabolic measurements will also be repeated using identical procedures and equipment.

**2.5.9 Outcome measures**

**Primary outcomes**
•Change from baseline to 6 months in carotid artery hemodynamic parameters.•Change from baseline in regional grey matter volume and TIV.•Change from baseline in DTI metrics of major white matter tracts.•Change from baseline in resting-state functional connectivity of the DMN, FPN, and SN (rs-fMRI).

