**Sequence 1: Structural MRI — Volumetric brain morphometry**

A T1-weighted three-dimensional Fast Spoiled Gradient Echo (FSPGR) sequence will be acquired for voxel-based morphometry (VBM) analysis. Imaging parameters will include repetition time (TR) = 7.8 ms; echo time (TE) = 3.1 ms; inversion time (TI) = 1010 ms; flip angle = 10°; field of view (FOV) = 256 × 256 mm; voxel size = 1 × 1 × 1 mm isotropic; 176 contiguous axial slices. Post-processing and analysis will be performed in MATLAB (MathWorks) using the SPM12 toolbox (Wellcome Centre for Human Neuroimaging, UCL) with the CAT12 (Computational Anatomy Toolbox, version 12) extension.
^
28
^ The standard CAT12 cross-sectional pipeline will be applied, comprising: (1) bias-field correction and denoising; (2) unified segmentation into grey matter (GM), white matter (WM), and cerebrospinal fluid (CSF) tissue classes; (3) diffeomorphic registration to the MNI152 standard space using the Geodesic Shooting algorithm (DARTEL); and (4) modulation of segmented images to preserve absolute tissue volumes following normalisation. For ROI-based segmentation, the CAT12 automated parcellation will be applied using the Automated Anatomical Labeling (AAL3) atlas, extracting absolute and relative grey matter volumes for bilateral regions of interest, including the hippocampus, entorhinal cortex, prefrontal cortex, anterior cingulate cortex, insula, and parietal association cortex. Total intracranial volume (TIV) will be extracted from the Jacobian determinant maps and used as a covariate in all volumetric analyses to account for individual differences in head size.

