**Sequence 2: Diffusion tensor imaging (DTI)**

White matter microstructural integrity will be assessed using a single-shot echo-planar DTI sequence acquired with participants in the supine position. Acquisition parameters will include TR = 4237 ms; TE = 87.3 ms; b-values = 0 and 1000 s/mm
^2^; 32 non-collinear diffusion gradient directions; FOV = 220 × 220 mm; voxel size = 1.72 × 1.72 × 2 mm; 45 axial slices; and GRAPPA acceleration factor = 2. DTI data will be pre-processed and analyzed using ExploreDTI.
^
29
^ Pre-processing will include: (1) signal drift correction; (2) Gibbs ringing suppression; (3) eddy current and subject motion correction using a robust tensor estimation approach with outlier rejection (REKINDLE algorithm); and (4) brain extraction. The diffusion tensor will be estimated at each voxel using a non-linear least squares fitting procedure. ROI-based tractography will be performed using deterministic streamline tractography (Euler integration, step size = 1 mm, FA threshold = 0.20, maximum turning angle = 30°). White matter tracts of primary interest — including the corpus callosum, corticospinal tract, superior longitudinal fasciculus, inferior fronto-occipital fasciculus, cingulum, and uncinate fasciculus — will be reconstructed using atlas-based ROI placement guided by the JHU white matter atlas. Mean values of fractional anisotropy (FA), mean diffusivity (MD), radial diffusivity (RD), and axial diffusivity (AD) will be extracted per tract per participant for between-group and pre-post comparisons.

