**2.3.6.6 Outcome measures**

**Primary outcomes**
•Carotid artery and superficial femoral artery diameter, PSV, EDV, RI, and endothelial shear stress (Doppler ultrasonography).•Regional grey matter volume and TIV (T1-weighted VBM).•FA, MD, RD, and AD of major white matter tracts (DTI).•Resting-state functional connectivity of the DMN, FPN, and SN (rs-fMRI).

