**2.5.10 Statistical analysis**

Pre- and post-intervention neuroimaging and cognitive outcomes will be compared using paired samples t-tests (or Wilcoxon signed-rank tests for non-normally distributed data). Mixed-effects linear regression models will be used to examine the longitudinal trajectory of outcome variables, adjusting for relevant covariates (age, sex, baseline physical activity, HbA1c, and medication use). The association between intervention-induced changes in neuroimaging metrics and changes in vascular, metabolic, and cognitive outcomes will be examined using partial correlations and multivariate regression. Effect sizes (Cohen’s d and partial η
^2^) will be reported for all primary outcomes.

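### Change in total intracranial volume (TIV) should not be a primary outcome, and the T1 pipeline for Phase 3 should be a within-subject one

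*Protocol article*

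**What the plan says.** All references are to the protocol article.

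- **Role of TIV (2.3.6.4, Sequence 1).** TIV is extracted from each T1 scan and "used as a covariate in all volumetric analyses to account for individual differences in head size".
- **Phase 1 primary outcomes (2.3.6.6).** The list includes "Regional grey matter volume and TIV (T1-weighted VBM").
- **Phase 3 primary outcomes (2.5.9).** The list includes "Change from baseline in regional grey matter volume and TIV".
- **T1 processing (2.3.6.4, Sequence 1).** "The standard CAT12 cross-sectional pipeline will be applied". The four steps that follow are correction, segmentation, registration to standard space and modulation. None registers a person's two scans to each other.
- **Phase 3 imaging (2.5.8).** After six months, "all participants will undergo a complete repeat of the neuroimaging protocol and cognitive assessments as described in Phase 1".
- **Phase 3 analysis (2.5.10).** "Pre- and post-intervention neuroimaging and cognitive outcomes will be compared using paired samples t-tests", or by signed-rank tests. Mixed models adjust for age, sex, baseline physical activity, HbA1c and medication use. Effect sizes are promised for every primary outcome.
- **Phase 3 design (2.5.2).** Pre-test post-test; no control arm is described.

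**The concern.** There are two separate matters.

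**TIV as an outcome.** The plan uses TIV to remove differences in head size from the volumetric comparisons. That presumes TIV is a stable property of the person and not something yoga acts on. Making its six-month change a primary outcome contradicts that role. With no control arm, a small systematic difference between the two scanning sessions would appear as a change in TIV. Under 2.5.10 it would be published with an effect size as a primary result.

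**The pipeline for change.** The cross-sectional pipeline suits Phase 1, which compares different people at one time. Phase 3 asks about change within a person. If each scan is processed separately, two separate processing errors enter every change score. The changes in question may be small: the Discussion already doubts that six months is long enough to detect macrostructural volume change in highly atrophied regions.

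**Working it through.** The plan gives no figure for TIV change, for the reliability of the volume measurements or for the Phase 3 sample size, so there is no stated number to reproduce here. The Phase 1 total of 80 (2.3.5) is not in question on this point.

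**Inputs**
- Two-sided α = 0.05, from 2.3.6.7; 2.5.10 does not restate it.
- Power 0.80, borrowed from 2.3.5.
- Phase 3 n: assumed. Section 2.5.3 makes Phase 1 participants eligible, while the 2.5.1 objective concerns the obese-diabetic group. Both n = 40 (that group) and n = 80 (everyone) are shown.
- Correlation r between the baseline and six-month volumes: assumed 0.90, 0.95 or 0.98.

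**Step 1: change in TIV when the true change is zero.** Let b be the systematic session shift divided by the SD of the paired difference. The paired t-test then has noncentrality b√n. At n = 40:

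| b | Probability that the test is significant |
|---|---|
| 0 | 5.0% |
| 0.1 | 9.5% |
| 0.2 | 23.5% |
| 0.3 | 45.7% |
| 0.5 | 86.9% |

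The first row agrees with a simulation of 20,000 null data sets with random error only, which rejected in 4.9%. Random error alone therefore keeps the test at its nominal level, but the test has nothing to find. Once there is drift, the test detects the drift.

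**Step 2: TIV in Phase 1.** A two-group comparison of TIV can be estimated. It says whether the groups differ in head size, which is useful for describing comparability. It does not measure a regional grey matter difference.

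**Step 3: whether the cross-sectional pipeline reaches Phase 3.** Section 2.3.6.4 places T1 processing under the heading of the neuroimaging protocol, and 2.5.8 repeats that protocol as described in Phase 1. The DTI text in the same section says that tract values "will be extracted per tract per participant for between-group and pre-post comparisons", so 2.3.6.4 is not written for Phase 1 alone. No other T1 processing is named. The carry-over is an inference from a cross-reference, since section 2.5 contains no sentence on it.

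**Step 4: what precision is at stake for regional volume.** With equal variances at the two visits,

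SD of change ÷ baseline SD = √(2(1 − r)).

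This gives √0.20 = 0.447, √0.10 = 0.316 and √0.04 = 0.200. The standardised paired difference detectable with 80% power is 0.454 at n = 40 and 0.317 at n = 80. Multiplying:

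| r (assumed) | SD of change | Detectable change, n = 40 | Detectable change, n = 80 |
|---|---|---|---|
| 0.90 | 0.447 | 0.20 | 0.14 |
| 0.95 | 0.316 | 0.14 | 0.10 |
| 0.98 | 0.200 | 0.09 | 0.06 |

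All entries are in baseline SDs.

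The gain from a within-subject pipeline depends on how far it raises r. From 0.95, the ratio of variances is 0.05/0.04 = 1.25 if r rises to 0.96, 0.05/0.03 = 1.7 if to 0.97, and 0.05/0.02 = 2.5 if to 0.98. The documents do not say which applies.

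**The case against.** The strongest reply concerns the pipeline. Section 2.3.6 is headed as baseline assessment for a cross-sectional phase, where a cross-sectional pipeline is appropriate. Section 2.5.8 can be read as repeating the scans only, and the pre-post wording belongs to the DTI paragraph, not the T1 paragraph. A journal article may also leave paired T1 processing to the full protocol. This stands in part: the carry-over is a reasonable reading but is not stated outright. What remains is that the only T1 method named is cross-sectional and that the cross-reference points to it.

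A reader might also draw four stronger conclusions that the documents do not support.

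- **That noise is tested as an effect throughout the volumetric analysis.** This fits change in TIV only. For regional grey matter, random processing error widens the SD of change and lowers power, but does not raise the false-positive rate. A systematic session shift could mimic an effect there too, but that is a consequence of the uncontrolled design and not of the pipeline alone.
- **That two different TIV values per person enter the Phase 3 adjustment.** Section 2.5.10 names paired tests, which carry no covariate, and a mixed-model covariate list without TIV.
- **That TIV would be regressed on itself.** Taken literally, adjusting every volumetric analysis for TIV would include the TIV outcome, and the group coefficient would then be exactly zero. The stated purpose, accounting for head size, points to adjustment of tissue volumes.
- **That TIV in Phase 1 is noise.** The no-change argument concerns six-month change and has no bearing on a comparison between groups.

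**Conclusion.** The point holds in two parts of unequal strength.

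The firmer part is that change in TIV is not a meaningful primary outcome. The plan's own use of TIV treats it as head size. If head size is fixed over six months, which is an assumption but one consistent with that use, a measured change can only be segmentation error or scanner or session drift. At an assumed n = 40, drift of 0.1 to 0.5 SD of the paired difference gives a significant result in 9.5% to 86.9% of trials. The documents give no estimate of drift. TIV in Phase 1 is a legitimate descriptive comparison but is misplaced among the primary outcomes.

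The second part is a matter of precision. The stated cross-sectional pipeline appears to apply to Phase 3 by cross-reference, and a within-subject pipeline is the better method for change. The size of the gain cannot be derived from the documents. The detectable change runs from 0.20 down to 0.09 baseline SD at n = 40, and from 0.14 down to 0.06 at n = 80, over assumed correlations of 0.90 to 0.98. Real differences between people in how much they change also lower the correlation, and no pipeline removes those.

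**What to change.** 1. In 2.3.6.6 and 2.5.9, remove TIV and change in TIV from the primary outcomes. Keep regional grey matter volume. Retain TIV as a covariate, and report it by group and by visit as a descriptive quality check.
2. In 2.5.8 or 2.5.10, state that the two T1 scans of each Phase 3 participant will be processed together with the CAT12 longitudinal (within-subject) pipeline, and confine the cross-sectional pipeline to the Phase 1 group comparison.
3. Wherever TIV adjustment is used in Phase 3, use a single TIV value per participant.

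**Cost.** No new scans or participants are needed, and the Data Availability statement says that no participant data have been collected. The wording must change. Because registration is complete and ethics approval is reported, altering the primary outcomes may also need a registry and ethics amendment. The baseline scans of Phase 3 entrants would have to be reprocessed through the longitudinal stream.
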